##### Assessment of the effectiveness

The QALYs, calculated from the EQ-5D questionnaire results, will be used as a measure of effectiveness. The QALYs will be estimated by calculating the area under the curve (AUC), which is obtained by summing up the areas of the geometrical shapes obtained by linear interpolation between the utility scores during the study period [35]. In addition, the baseline utility will be controlled using a regression-based adjustment, since there tends to be a strong correlation between the baseline utility of patients and the QALY scores [35].

##### Cost assessment

Only direct unit costs per patient will be calculated. Indirect (caregivers, etc.) and intangible costs will not be considered for the analysis. The specific costs that will be taken into account include: costs directly associated with the telemonitoring intervention (cost of purchase and maintenance of the system, training of professionals in the use of the system, salaries of the health care professionals), costs associated with the home care (visits and telephone calls), costs related to the impact of the telemonitoring program on the necessary resources for the provision of patient care (number of visits to a primary care doctor, visit to the emergency department, number of hospital admissions). The costs will be based on 2009 figures and will be expressed in euros.

Health resources use estimates will be measured considering the following variables: number of telephone consultations (both control calls and calls made as a result of alerts) made or received by health care professionals (by the GP or nurse), average duration of telephone consultations, number of home care visits (both control visits and visits due to alerts) performed by health care professionals (by the general practitioner or nurse), average time spent by health care professionals to check the telemonitoring data daily, number of primary care visit, number of emergency department visits, number of visits to the specialist doctors and number of hospital admissions. The time taken to check telemonitoring data daily or undertaken monitoring telephone calls will be estimated by timing a sample of these tasks.

Resource use estimates will be combined with unit costs per patient obtained as follows: the time spent by health care professionals in made and answered telephone consultations and in checking the telemonitoring data daily, will be assessed based on the salaries for nurses and GPs as reflected in the Basque Health Service wage payment tables; primary care visits, emergency department visits and visits to the specialist doctors, will be amounted in accordance with the Osakidetza billing rates for health care services; hospital admissions will be assessed according to Diagnostic Related Groups (DRGs) for each pathologic condition; telemonitoring equipment (software and devices) will be assessed based on their equivalent annual cost, maintenance and training for their management will be valued using the market price provided by the supplier.

The cost of telecommunications and computer equipment will not be considered, since this is an already implemented infrastructure in the Basque Health System, which is used for many other applications and daily tasks in addition to the telemonitoring process. The cost per patient will be minimal and, therefore, ignored in the costs calculation.

As the comparison is restricted to the programs under study, costs common to both need not be considered as they will not affect the choice between the given programs.

The costs will be based on 2009 figures and will be expressed in euros. The discount-rate used to calculate the equivalent annual cost will be 3%.

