Home telemonitoring has been found to reduce rates of hospitalisation and emergency department visits for chronic obstructive pulmonary disease (COPD) patients, while findings for hospital bed days were not consistent and varied between studies [15,16]. There was a higher mortality-rate among patients with COPD using home telemonitoring compared with usual care, but the number of original studies was scarce and the sample sizes were relatively small. Hence, the outcomes must be interpreted cautiously [15,16]. According to recent systematic reviews, telemonitoring interventions for patients with HF have been shown to be effective in reducing the risk of all-cause mortality, HF-related hospitalisations and emergency department visits [15,17-19]. Moreover, the use of home telemonitoring for patients with HF improved quality of life, patient self-care and evidence-based prescribing [15,17-19]. However, further studies of high methodological quality are required to give more precise information about the potential clinical benefits of home telehealth interventions prior to scaling-up the use of the new technology [7,19].

The telemonitoring system used in the present study is based on a telemonitoring system employed in another hospital-based clinical trial [20]. The home telemonitoring system has been successfully tested on patients with HF and COPD in a randomised controlled trial carried out in Donostia University Hospital (Basque Country), *Current Controlled Trials *ISRCTN62033748. In contrast to the aforementioned trial, in the present study the management of the telemonitoring intervention is carried out by primary care nurses and general practitioners (GPs). To the best of our knowledge, no other primary care-based tele-homecare studies have been undertaken with regards to the type of patients and the telemonitoring procedure employed in this investigation.

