### Intervention

#### Description of the intervention

In the IG, telemonitoring will consist of daily transfers of the following self-measured clinical parameters: respiratory-rate, heart-rate, blood pressure, blood oxygen saturation using pulse oxymetry, weight and body temperature. Together with the clinical data, patients will also complete a brief questionnaire aimed at assessing the patient's perception of his/her medical and functional condition. The questionnaire also contains items concerning compliance with medication and diet. Health professionals will check the data daily and will routinely contact the patient by phone every two weeks (nursing staff). Other telephone contacts will be carried out, if necessary, if the data received at the primary health care centre are out of the established limits. The telemonitoring system comprises personalised alerts set for each patient, with messages being sent to a Web-based platform when the recorded parameters fall outside established limits (which may be adjusted over time).

We have established standard initial threshold values for all the telemonitored parameters, which can be further modified by health care professionals according to the specific characteristics of the patients. The established threshold values are essential for the monitoring of the patient's condition and for the detection of unusual changes. When the measurements fall outside the established limits, alerts will be triggered via the PDA terminal and the clinical staff will act according to the medical condition of the patient. Alternatively, the patients will be advised to call the emergency services at the weekends and at times when the health centres are closed.

The standard threshold values for alerts are shown in Table 1.

**Table 1 T1:** Established thresholds for the telemonitored parameters.

Telemonitored parameters	Established threshold values
Respiratory-rate	< 12 or >24 breaths per minute (bpm)
Heart-rate	< 50 or >100 beats per minute (bpm)
Systolic blood pressure	< 100 or >160 millimeters of mercury (mmHg)
Diastolic blood pressure,	< 60 or >95 millimeters of mercury (mmHg)
Oxygen saturation	< 95% (this is a frequently adjusted limit for patients with CLD)
Temperature	> 37°C
Weight	Should be notified if there is an increase of 1 Kg in three days

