### Study variables

#### Initial assessment and baseline data

The following *socio-demographic data *will be collected for every patient taking part in the study: health centre, assigned GP and nurse, date of birth and age, gender, living arrangements, main caregiver and relationship with the caregiver, level of education and the existence of any adverse social factors (*i.e*.: poverty, social exclusion, loneliness, lack of support, isolation, recent widowhood).

The following *clinical variables *will also be recorded: main disease (HF and/or CLD), degree of severity of the disease (based on the FEV1 - forced expiratory volume in one second- for COPD and on the NYHA - New York Heart Association- classification and the ejection fraction for HF. Severity of illness measures will be collected at the moment of enrolment from the clinical records depending on availability and will be used to ensure comparability between the two groups), requirement for home oxygen therapy, name and list of the drugs taken regularly, adherence to the prescribed medication (compliance) using the four-item self reported scale proposed by Morinsky *et al. *[21], the Barthel Index (BI) [22], the EuroQol questionnaire (EQ-5D) [23-25], and the Zarit Burden Interview (ZBI) [26-28].

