#### Outcome measures

All the outcome measures will be collected after 3, 6 and 12 months of follow-up, except for satisfaction with the telemonitoring technology, which will be measured only once (approximately after 3 months from the start of the study). Table 2 shows a summary of the outcome variables that will be evaluated in the present study.

**Table 2 T2:** Summary of the outcome measures analysed in the study.

	Primary outcome measure	Secondary outcome measures
**Mortality**		- Mortality due to any cause
		- Mortality due to HF or CLD
		
**Use of health care resources**	- Hospital admissions due to any cause	**- **Hospital admissions due to HF or CLD
		- Duration of hospital stay
		- Emergency department visits
		- Home visits by GP or nurses
		- Visits to primary care centres by family or caregivers
		- Telephone contacts with professionals
		- Visits to specialist doctors
		
**Clinical efficacy**		- Worsening of the patients' pulmonary and/or heart condition (number of episodes)
		
**Functional status and quality of life**		- Patient Quality of Life (EQ-5D questionnaire)
		- Functional status (Barthel Index)
		- Caregiver burden (Zarit Burden Interview)
		
**Cost-effectiveness**		- Cost-effectiveness (using QALYs)
		
**Satisfaction with the new technology**		- Degree of satisfaction of patients and health care professionals
		
**Compliance**		- Patient and provider compliance with the telemonitoring

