##### 2. Secondary outcome measures

2.1 *Duration of hospital stay: *number of bed-days for emergency admissions with a primary diagnosis of HF, CLD (*i.e*., COPD, asthma and other respiratory conditions) and other causes during 12 months after randomisation.

2.2 *Number of hospital admissions due to exacerbation of HF and CLD *(*i.e*., *COPD, asthma and other respiratory conditions*) that occurred in a period of 12 months post-randomisation.

2.3 *Mortality rate: *number of all-cause deaths at 12 months. Cause of death will be taken from the primary and/or secondary care clinical records.

2.4 *Level of use of health resources measured during a period of 12 months after randomisation:*

- Number of emergency department visits for a cardiac or respiratory cause and for all causes.

- Number of home visits (by their GP or nurse).

- Number of primary care visits.

- Number of telephone contacts with primary health care professionals.

- Number of visits to the specialist doctors.

2.5 *Cost-effectiveness analysis*. The costs associated with the health care resources used will be estimated based on the following variables: duration of hospital stay, use of emergency services, purchase and maintenance of telemonitoring devices, number of consultations and time of the health care personnel, as well as the time dedicated by the health care professionals to using the telemonitoring equipment. The effectiveness will be expressed in Quality-Adjusted Life Years (QALY) and will be calculated from the data of the Health Related Quality of Life (HRQL) obtained from the generic EQ-5D questionnaire.

2.6 *Health related quality of life (HRQL)*. The validated Spanish version of the EQ-5D questionnaire will be employed for the quality of life assessment [23-25]. This questionnaire describes the health status in five dimensions (mobility, self-care, usual activities, pain/discomfort, and anxiety/depression) with three possible responses for each item and using the visual analogue scale (VAS) ranging between 0 and 100.

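### Outpatient drugs and home oxygen are recorded only at baseline and never enter the costing, so the ICER may omit a cost that differs between the arms

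*Protocol article*

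**What the plan says.** Under Initial assessment and baseline data, the clinical variables recorded at enrolment include "requirement for home oxygen therapy, name and list of the drugs taken regularly". Under Outcome measures, the follow-up rule is "All the outcome measures will be collected after 3, 6 and 12 months of follow-up", with satisfaction as the only exception. Neither drugs nor oxygen appears in Table 2 or in outcomes 2.1 to 2.11.

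The costing is described in two places. Secondary outcome 2.5 bases costs on "duration of hospital stay, use of emergency services, purchase and maintenance of telemonitoring devices, number of consultations and time of the health care personnel", plus staff time spent on the telemonitoring equipment. Cost assessment then gives cost categories, a list of measured resources ending in "number of primary care visit, number of emergency department visits, number of visits to the specialist doctors and number of hospital admissions", and a source of unit cost for each item. Admissions are valued by DRG.

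Cost assessment also says what is left out: indirect and intangible costs; telecommunications and computer equipment, with a reason; and shared costs, because "costs common to both need not be considered as they will not affect the choice between the given programs".

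On how treatment might change, the Background reports from systematic reviews that home telemonitoring in heart failure "improved quality of life, patient self-care and evidence-based prescribing". Description of the intervention says that when readings fall outside limits, "the clinical staff will act according to the medical condition of the patient".

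**The concern.** A cost may safely be left out of an incremental analysis if it is the same in both arms. For outpatient treatment the protocol does not claim this, and its own rationale gives reason to doubt it: it cites an effect on heart failure prescribing and expects telemonitoring to help compliance and early response to deterioration.

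Followed as written, the analysis credits each avoided admission at its DRG value and prices at zero any outpatient drug or oxygen treatment that accompanied the avoidance. It equally gives no credit if treatment use falls. The incremental cost, the ICER and the proportion of bootstrap replicates under 30,000 euro/QALY would all carry that gap. Cost-effectiveness is a named secondary objective. If the use is not recorded during the trial, it may not be recoverable afterwards.

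**Working it through.** The protocol gives no drug price, oxygen price or QALY difference, so there is no figure to reproduce. The check is a comparison of lists, followed by a calculation on assumed values to show the scale.

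**Step 1: where the items appear.**

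| Place in the protocol article | Outpatient drugs | Home oxygen |
|---|---|---|
| Initial assessment and baseline data | Yes (regular drugs) | Yes (requirement) |
| Table 2 and outcomes 2.1 to 2.11 (3, 6, 12 months) | No | No |
| Outcome 2.5, cost variables | No | No |
| Cost assessment, cost categories | No | No |
| Cost assessment, measured resources | No | No |
| Cost assessment, unit-cost sources | No | No |

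The only medication information planned after baseline is the set of compliance items in the daily questionnaire. That questionnaire is completed by the intervention group only, and it records compliance rather than drugs used. Drugs given during an admission may be covered by the DRG value, so the gap concerns outpatient use.

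**Step 2: is the omission covered by a stated exclusion?** Outpatient drugs and oxygen are direct health care items, so the exclusion of indirect and intangible costs does not reach them. They are not telecommunications or computer equipment. That leaves the rule on costs common to both programmes, and the protocol nowhere says they are common.

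**Step 3: does the uncertainty analysis expose the gap?** Presentation of the economic analysis relies on non-parametric bootstrapping. This resamples the costs and QALYs collected for each patient. A cost that is never collected is absent from every replicate, so neither the confidence interval nor the acceptability curve can reflect it.

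**Step 4: scale, on assumed values.** Let d be the omitted cost difference per patient-year (intervention minus control) and q the QALY gain.

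- Shift in ICER = d / q
- QALY equivalent at the threshold = d / 30,000

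| d (euro, assumed) | q = 0.01 | q = 0.02 | q = 0.05 | q = 0.10 | d / 30,000 (QALY) |
|---|---|---|---|---|---|
| 50 | 5,000 | 2,500 | 1,000 | 500 | 0.0017 |
| 100 | 10,000 | 5,000 | 2,000 | 1,000 | 0.0033 |
| 300 | 30,000 | 15,000 | 6,000 | 3,000 | 0.010 |
| 1,000 | 100,000 | 50,000 | 20,000 | 10,000 | 0.033 |

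For example, 300 / 0.02 = 15,000 euro/QALY, half the threshold, and 50 / 0.10 = 500 euro/QALY, which is negligible. A negative d gives the same values with the sign reversed, and d = 0 gives no shift.

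**The case against.** The best defence has four parts.

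- **The described response to alerts is costed.** The protocol describes telephone contacts, and calls and home visits prompted by alerts, and Cost assessment counts these. This stands. A reader might infer that alerts are meant to change drugs or oxygen, but the text names no treatment as the response.
- **The evidence for a treatment effect is thin.** The prescribing statement concerns heart failure only, comes from outside reviews and says nothing about cost. Nothing says telemonitoring changes oxygen use or prescribing in chronic lung disease. Professionals in both arms attend the same workshop on disease management and early detection of relapse, which could narrow any difference. This also stands. The documents make a cost difference plausible for heart failure drugs but do not establish one.
- **The direction is unknown.** A reader might infer that the omission must favour telemonitoring, because treatment that prevents admissions is counted as free. Fewer or milder exacerbations could equally reduce short treatment courses, so the documents do not support that inference.
- **The perspective may exclude these payments.** The analysis takes the health care provider's view, and the protocol does not say who pays for outpatient drugs or oxygen. If the provider does not, leaving them out of the base case is legitimate. The protocol does not give this as its reason.

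It could also be said that a journal article condenses the full protocol, and that the cost categories are worded as what the costs include. That carries little weight here. The resource list is presented as the set of variables to be measured, goes down to average call duration and timed samples of data checking, and each item has a unit-cost source. This is a stated scope rather than abbreviated detail.

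**Conclusion.** The point holds in a limited form. Outpatient drug and home-oxygen use is neither followed up nor costed, no reason is given, and the protocol's own rule for leaving costs out does not clearly cover it. Given the cited effect on heart failure prescribing, the ICER and the acceptability curve may omit a cost that differs between the arms.

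The size and sign of the effect cannot be determined from the document. The assumed range of 500 to 100,000 euro/QALY in either direction shows that the omission could be trivial or decisive against 30,000. It is not evidence that the effect is large. Both that range and its relevance depend on there being a cost difference and on the provider, or the chosen scenario, bearing it. The primary outcome and its analysis are not affected.

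**What to change.** Record outpatient drugs (regular drugs and short courses) and home-oxygen use in both arms at 3, 6 and 12 months. Take them from the primary care records if those hold the information. The protocol describes the Osabide database only as a means of identifying patients, so this must be checked first. If the records do not hold it, collect the data at the planned follow-up assessments. Add both items, with unit prices and their source, to the resource and cost lists in Cost assessment and to outcome 2.5, so that they enter the bootstrap.

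If the provider perspective is held to exclude these payments, say so, keep that as the base case, and report a scenario analysis that includes them.

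The cost is protocol wording, repeating for 60 patients a list already taken at baseline together with short courses, and obtaining unit prices. The resulting ICER may be less favourable to telemonitoring.

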Qualitative questionnaire	Negative answers to the questionnaire which correspond to: feeling worse, breathing difficulties, increased nocturia, oedema, worsening of cough, increased sputum production and a change in sputum colour

In the CG, patients will receive usual care, consisting of regular medical examinations in line with the established programmes for monitoring home-based patients. The frequency of the medical examinations will vary depending on the clinical, social and family situation of each patient. Additionally, the GP and/or nurse will see or call the patient on demand in the event of a deterioration in the medical condition. Note that the IG will receive usual care, as well as the extra telemonitoring specified under the study protocol.

Prior to the intervention, all GPs and nurses in charge of the care of the participating patients (in both IG and CG) will attend a 4-hour workshop on the management of HF and COPD and early detection of relapses. Additionally, the health care professionals involved with the IG will receive further training on the use of the telemonitoring system. The key activities for the CG and IG are outlined in Figure 2.

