#### Economic analysis of the telemonitoring intervention

A cost-effectiveness analysis will be undertaken from the perspective of the health care provider. The time horizon will be of one year.

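### Unit costs are on mixed bases (wage tables for telemonitoring's staff time, billing rates for visits, DRGs for admissions), which may favour telemonitoring in the ICER, and the planned bootstrap would not show it

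*Protocol article*

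**What the plan says.** The economic section adopts a single perspective: "A cost-effectiveness analysis will be undertaken from the perspective of the health care provider". Within it, the Cost assessment section of the protocol article uses several price sources:

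- Staff time: "the time spent by health care professionals in made and answered telephone consultations and in checking the telemonitoring data daily" is the time to be valued, and it "will be assessed based on the salaries for nurses and GPs as reflected in the Basque Health Service wage payment tables".
- Primary care, emergency department and specialist visits: their cost "will be amounted in accordance with the Osakidetza billing rates for health care services".
- Admissions: "hospital admissions will be assessed according to Diagnostic Related Groups (DRGs) for each pathologic condition".
- Telemonitoring equipment: equivalent annual cost. In addition, "maintenance and training for their management will be valued using the market price provided by the supplier".
- Home visits: the resource list counts the "number of home care visits (both control visits and visits due to alerts) performed by health care professionals" as a separate item, but the unit-cost paragraph names no source for them.

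The same section leaves out telecommunications and computer equipment as infrastructure already in place. Under Description of the intervention, staff look at the transmitted data every day and nurses phone each intervention patient every two weeks. There, too, "the health care professionals involved with the IG will receive further training on the use of the telemonitoring system". Under Presentation of the economic analysis, the one sensitivity analysis named is a non-parametric bootstrap, and results are judged against 30,000 euro/QALY.

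**The concern.** One ratio combines staff time taken from a pay table with services taken from a tariff. If a tariff price contains employer contributions, premises, administration and support staff, and the pay-table figure does not, then an hour spent on a call or a data check is priced lower than an hour inside a visit. This would not be neutral between arms. Daily checks and routine fortnightly calls exist only in the intervention arm, while emergency, primary care and specialist visits are among the outcomes that the secondary objectives expect the intervention to affect.

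The ICER and the share of bootstrap replicates under the threshold could then reflect the price basis as well as resource use. The bootstrap resamples patients at fixed unit costs, so its interval, plane and acceptability curve would carry any such effect unchanged. Cost-effectiveness is a named secondary objective with a stated decision threshold. The primary outcome is not touched.

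**Working it through.** The protocol gives no unit cost, task time, expected cost difference, QALY gain or ICER, so there is no stated figure to reproduce. The check covers direction and an illustrative size.

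**Symbols.** H = staff hours that telemonitoring adds per patient-year; w = salary per hour; k = ratio of full cost to salary; D = difference in visits (intervention minus control); b = billing rate per visit, taken here to be a full-cost price.

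**Direction.** Incremental cost of staff time plus visits:

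- Plan's mixed basis: H·w + b·D
- All at full cost: k·H·w + b·D
- All at salary: H·w + (b/k)·D

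Full cost minus mixed is (k − 1)·H·w, which is positive whatever D is. Mixed minus salary is b·D·(1 − 1/k), which is negative if visits fall and positive if they rise.

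With assumed values H = 25.2, w = 20 euro, k = 1.6 and b = 60 euro (so H·w = 504 and b/k = 37.5), in euro per patient:

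| D | Mixed | All full cost | All salary |
|---|---|---|---|
| −5 | 504 − 300 = 204 | 806 − 300 = 506 | 504 − 187.5 = 316.5 |
| 0 | 504 | 806 | 504 |
| +5 | 504 + 300 = 804 | 806 + 300 = 1,106 | 504 + 187.5 = 691.5 |

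Against an all-full-cost analysis the mixed basis always favours telemonitoring. Against an all-salary analysis it does so only if visits fall.

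**Size.** From the protocol: daily checks, and a call every two weeks (about 26 a year). Assumed: 250 to 365 checking days, 2 to 10 minutes per check, 5 to 15 minutes per call, w = 15 to 25 euro, k = 1.3 to 2.0. Alert-triggered calls are left out because no number is given.

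- Low: H = (250×2 + 26×5)/60 = 10.5 h; at 15 euro this is 158 euro; the extra at k = 1.3 is 0.3×157.5 = 47 euro.
- High: H = (365×10 + 26×15)/60 = 67.3 h; at 25 euro this is 1,683 euro; the extra at k = 2.0 is 1,683 euro.

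Dividing by an assumed QALY gain gives the shift in the ICER:

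- Gain 0.02: 47/0.02 is about 2,400, up to 1,683/0.02, about 84,000 euro/QALY.
- Gain 0.05: about 900 up to about 34,000 euro/QALY.

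Set against 30,000 euro/QALY, this runs from trivial to decisive.

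**Training.** The sentence that applies salaries covers calls and data checking only, so attendance at the intervention-only training has no explicit unit cost. If one GP and one nurse per intervention patient attended for an assumed 2 to 4 hours each, that is 4 to 8 hours, or 100 to 200 euro at an assumed 25 euro/h, before annualisation.

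**The case against.** The strongest reply is that the premise is inferred. The article does not say whether the wage figure will include employer contributions, or what the billing rates contain. Timing a sample of tasks and applying pay is ordinary micro-costing where no tariff exists for the task, and using a tariff where one exists is equally ordinary. The protocol also takes a marginal view of shared infrastructure. All of this stands, and it is why the point is conditional. It does not remove the point, because the mixture is a stated valuation rule and nothing stated tests it.

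Three stronger readings are tempting, and the document does not support them:

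- *The tilt is certain, because an added staff hour is always priced below a saved one.* Prices attach to activities, not to arms. Control patients can also be phoned on demand, so a saved call is priced at salary too, and an added visit at the billing rate. Only the checks and the excess calls belong to telemonitoring.
- *The savings sought are all priced at billing rates.* The main saving sought is in admissions, which are DRG-valued. Home visits, important for this population and partly alert-driven, have no explicit price source.
- *Valuing training at the supplier's price is itself a bias.* A market price is not an undervaluation. What remains is trainees' time, and even that may be covered: the general list of intervention costs names both training and professionals' salaries.

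The amount may also be small beside the savings sought. The planned reduction is 0.35×3.5 = 1.225 admissions per patient, so 47 to 1,683 euro corresponds to about 39 to 1,374 euro per admission averted.

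**Conclusion.** The point holds in a limited form. Staff time, visits and admissions enter one provider-perspective ICER on different price bases, and the activities priced from wage tables include work that only telemonitoring adds. If the billing rates carry employer costs and overheads that the wage tables lack, this added work is under-costed relative to the tariff-priced services. The ICER and the proportion under 30,000 euro/QALY may then favour telemonitoring.

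The direction is firm only against an all-full-cost analysis under that condition. The size cannot be derived from the protocol: 47 to 1,683 euro per patient-year rests on assumed minutes, pay and overhead ratio, with only the frequency of checks and calls taken from the document. That the bootstrap leaves unit costs untouched does not depend on these assumptions.

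**What to change.** In Cost assessment:

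1. Value staff time for calls, data checking and attendance at the intervention-only training at full cost per staff-hour: salary plus employer contributions and overheads, consistent with what the billing rates contain. State what both price sources include.
2. Name the unit cost for home visits and put it on the same basis.

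In Presentation of the economic analysis:

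3. Add a deterministic sensitivity analysis on unit costs beside the bootstrap, including a version with staff time at salary only, and report the ICER and the proportion under 30,000 euro/QALY for each.

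This needs no new patient data, only an overhead factor from the health service's accounts and the training attendance list. The downside is a little more costing work and a slightly higher, so less favourable, intervention cost.
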